## Abstract

**Purpose:**

A majority of adolescents between the ages of 13 and 17 use at least one social media platform for interactive engagement. This age group marks a crucial period of social development, given the high susceptibility of young minds to influence. Excessive use of social media is associated with severe public health concerns, such as alcohol abuse, interpersonal dysfunction, and sexual behaviour-related concerns. This protocol details the development of a school-based social marketing intervention (SMI) and implementation of RCT to evaluate the effectiveness of SMI to reduce excessive social media use and associated adverse effects.

**Methods:**

The study will employ an open-label, cluster-randomized controlled trial (RCT) design. The study will be conducted in senior secondary schools located in three cities in Northern India (Chandigarh, Panchkula, and Mohali). A total of 12 schools will be selected, comprising four schools from each study area. Within each city, schools (clusters) will be randomized into intervention and control arms. Based on the available literature on sample size guidelines for Randomized Controlled Trials (RCTs), the total sample size is estimated to be 1260 students for all three cities. The SMI will be delivered in three phases: a pre-intervention assessment phase, a three-month intervention phase guided by the COM-B model of behavioural change, and a post-intervention evaluation phase to measure outcomes in both groups.

**Discussion:**

The adolescent relationship with social media is complex, providing both chances for learning and risks of misinformation and unhealthy behaviours. This study protocol aims to outline our plan to evaluate whether a structured SMI can enhance awareness and reduce adverse behaviours related to alcohol use, sexual health, and interpersonal relationships among adolescents.

**Trial Registration:**

Clinical Trial Registry-India, CTRI/2024/11/077115, originally registered on 11/11/2024.

## Introduction

Social media is now a fundamental part of everyone’s daily lives, particularly among adolescents [1]. Nearly 95% of adolescents use at least one social networking site, with 45% reporting they are online ‘almost consistently’ [2]. An Indian study also shows that almost 90% of adolescents have either a moderate or high level of social media addiction [3]. This constant exposure to the digital sphere makes it a critical public health concern.

The unregulated content of social media has a huge impact on the impressionable minds of teenagers. Numerous studies have linked excessive social media use among adolescents to a range of adverse outcomes, including alcohol abuse, disrupted family relationships, and risky sexual behaviours [4–6]. Early alcohol use among teenagers is associated with serious consequences, such as self-harm, aggression, and academic failure, with global DALYs for adolescent alcohol use coming to 2.80 billion in 2023 [7]. Also, Child-family relationships are adversely affected due to the time spent on social media by adolescents. There may be family disconnectedness, conflicts, lack of direct open communication, absence of cohesion, etc [8]. Exposure to sexualized content also poses risks; approximately 74.2% of the adolescents reported high or very high exposure to sexual content on social media that influences their sexual behaviour. Studies have found a link between media exposure and early initiation of sexual activity, which can lead to unintended pregnancies and increased vulnerability to sexually transmitted infections (STIs) [8].

While substantial research has been conducted in high-income countries to understand the relationship between social media use and adolescent behaviour, there is a growing need to explore these patterns in low- and middle-income countries (LMICs) like India, with an explosion of digital devices in a few years and a lack of school-based digital literacy programs. This demands culturally relevant, evidence-based interventions that can be easily implemented in a school curriculum.

The present protocol aims to investigate how a social marketing intervention will influence alcohol use, risky sexual behaviours, and adverse child-family relationships among school-going adolescents in India. Social marketing intervention (SMI) will be designed to promote healthier behaviours and equip adolescents with media literacy skills, refusal self-efficacy, and digital resilience. By leveraging the same persuasive techniques used in advertising, it can serve as a powerful tool to encourage positive behavioural change. The Social Marketing Intervention (SMI) will be developed through the collective contribution of stakeholders and will be pre-tested for maximum impact. The multi-cluster randomized controlled trial (RCT) will be employed to accurately assess effectiveness. Additionally, an economic evaluation will estimate the cost-effectiveness of the intervention, providing evidence for its sustainability and scalability within the existing programs, like the Ayushman Bharat School Health and Wellness Programme (SHWP).

## Methods

### Study aim and design

The study will employ an open-label, cluster-randomized controlled trial (RCT) design to investigate and evaluate the effects of a social marketing intervention for adverse child-family relationships, alcohol use disorders, and sexual health issues attributable to social media usage among school-going adolescents.

A SPIRIT schedule of the study design can be found in Fig 1.

**Fig 1 pone.0354663.g001:**
[figure not shown]
SPIRIT schedule and timeline.

### Study area and settings

The study will be conducted in senior secondary schools located in three cities in Northern India (Chandigarh, Panchkula, and Mohali). A total of 12 schools will be selected, comprising four schools from each study area. Within each city, schools (clusters) will be randomized into intervention and control arms (Fig 2). The protocol paper has been prepared following SPIRIT 2025 guidelines (S1 File).

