#### Sampling strategy for baseline assessment.

In total, 1260 adolescents will be recruited from 12 schools (4 schools per city) across three cities in Northern India (Fig 3). These four schools per city will be divided into two government schools and two private schools for socio-economic representation. Each city will recruit 420 adolescents, 105 students per school. We will randomly select 4 classes from the pool of eligible 9^th^-, 10^th^-, 11^th^, and 12th-grade classes, assuming an average class size ranging between 25 and 35 students.

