### Phase 2: The Intervention Phase

#### Sample size for the intervention phase.

For Phase 2, based on the available literature on sample size guidelines for Randomized Controlled Trials. [17], for a 95% confidence level for the two-tailed hypothesis (${\text{Z}}_{\alpha }$= 1.96) and to achieve a power of 90% (${\text{Z}}_{\text{1}-\beta }$ = 1.2816), with an assumed standard deviation of population 0.15 and estimated effect size (D) of 5%, a minimum sample size of 189 per arm/group is required for the study, as per the following for the cluster-level randomization:

$$\begin{array}{c} \text{n}=\frac{{\;\text{2}\left({\text{Z}}_{\alpha }+{\text{Z}}_{\text{1}-\beta }\right)}^{\text{2}}\sigma^{\text{2}}}{(D{)}^{\text{2}}} \end{array}$$

By considering an attrition rate (10%), the sample size for each group (control and intervention) has come out to be approximately 208 participants in each of the control and intervention groups. Therefore, the minimum sample size for both control and intervention groups comes out to be 416 per study location. The total sample size is estimated to be n is equal to 1248, including all three cities in Northern India. To align with the baseline sample size, the RCT will also include 1,260 participants across all three cities.

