#### Sampling strategy for randomized controlled trial.

The same COHORT from the pre-intervention phase (baseline assessment) will be followed. Therefore, the 12 schools will be randomly selected into 6 intervention groups and 6 control groups, as shown in Fig 2.

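### School randomisation is restricted by city only, although each city has two government and two private schools, so school type is left to chance imbalance between arms

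*Protocol article*

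**What the plan says.** The section Study area and settings gives the number of clusters, "A total of 12 schools will be selected, comprising four schools from each study area", and the allocation rule, "Within each city, schools (clusters) will be randomized into intervention and control arms". The Methods part of the abstract repeats that rule. City is the only restriction named.

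The section Sampling strategy for baseline assessment fixes the school mix: "These four schools per city will be divided into two government schools and two private schools for socio-economic representation". It also sets the numbers, "Each city will recruit 420 adolescents, 105 students per school", and describes the choice of classes: "We will randomly select 4 classes from the pool of eligible" classes of grades 9 to 12.

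The section Sampling strategy for randomized controlled trial states that "the 12 schools will be randomly selected into 6 intervention groups and 6 control groups, as shown in Fig 2". It mentions neither city nor school type.

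The Statistical analysis section plans generalized estimating equations (GEE) for changes in outcomes, adjusted for socio-demographic and economic variables. School type is not named among them. The model equations are in a supplementary file that is not shown.

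**The concern.** The protocol treats school type as a socio-economic marker when it samples schools and then does not carry it into the allocation. With only 12 randomised units, a factor left out of the restriction has a good chance of ending up uneven between arms. Government and private schools could plausibly differ in device access, family circumstances and alcohol exposure, all of which bear on the outcomes.

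At stake are the precision of the comparison and how convincing the result is to a reader who sees, for example, five government schools in one arm and one in the other. An analysis plan written later can adjust for school type, but it cannot balance an allocation that has already been made. That is why the point belongs to the protocol and is not a detail to be left for later.

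**Working it through.** **The plan's own figure.** Inputs from Sample size for the intervention phase: z-values 1.96 and 1.2816, SD 0.15, D = 0.05.

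- n = 2 × (1.96 + 1.2816)² × 0.15² / 0.05² = 189.1, stated as 189 per arm.
- With 10% attrition: 189 × 1.1 = 208 per arm, 416 per city, 3 × 416 = 1248, raised to 1260 (12 × 105).

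The plan's figure is reproduced. The article gives no figure for balance by school type.

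**Allocation ratio within a city.** It is not stated, but "the minimum sample size for both control and intervention groups comes out to be 416 per study location" means about 208 per arm in each city. At 105 students per school, two schools per arm give 2 × 105 = 210. So 2:2 per city is implied.

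**One city.** Choosing 2 intervention schools from 4 gives C(4,2) = 6 allocations. The number of government schools among them is 0, 1 or 2 in 1, 4 and 1 allocations. Both intervention schools are of one type in 2/6 = 1/3.

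**At least one of three cities.** 1 − (2/3)³ = 19/27 = 70.4%.

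**Whole trial.** There are 6³ = 216 allocations. The counts for 0 to 6 government schools in the intervention arm are the coefficients of (1 + 4x + x²)³: 1, 12, 51, 88, 51, 12, 1.

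| Split of school type in the intervention arm | Allocations | Probability |
|---|---|---|
| 3:3 | 88 | 40.7% |
| 4:2 either way | 102 | 47.2% |
| 5:1 either way | 24 | 11.1% |
| 6:0 either way | 2 | 0.9% |

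Not 3:3: 128/216 = 59.3%.

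**Effect on a raw difference.** If the two school types differ by d points, and the intervention arm has g government schools out of 6 while the control arm has 6 − g, the raw difference shifts by d × (2g − 6)/6. The article gives no d, so it is an assumption; I take 5 to 15 points. At the planning SD of 0.15 that is 0.33 to 1 SD, so the upper end is a large difference.

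- 4:2 split: d/3 = 1.7 to 5.0 points.
- 5:1 split: 2d/3 = 3.3 to 10 points.

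The target effect is 5%. These shifts apply to an unadjusted contrast of levels, not to change from baseline.

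**Cost of adjusting afterwards.** In a linear school-level model with equal school sizes, adding school type multiplies the variance of the arm effect by 1/(1 − r²) relative to a balanced allocation, where r is the correlation of arm and type over 12 schools.

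- 4:2: r = 4/12 = 1/3, factor 1.125.
- 5:1: r = 8/12 = 2/3, factor 1.8.
- 6:0: r = 1, so the two effects cannot be separated.

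**With one school of each type per arm in every city.** There are 2⁶ = 64 allocations, all 3:3. The chance of imbalance by type is 0.

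**The case against.** The strongest reply is that chance imbalance under valid randomisation is not bias, and that the analysis already handles much of it. The GEE models change from a baseline assessment, so a stable difference in level between school types would largely drop out, and socio-economic adjustment may absorb part of the rest. This stands. The raw shifts are therefore upper guides to what would remain in the estimate, and the usual imbalance (4:2) would cost only 12.5% in variance once type is in the model. But school type is not a named covariate, and types may also differ in how outcomes change over time.

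A second reply is that Figs 2 and 3 are not visible and may show allocation by school type. This also stands and limits confidence. The visible rule still names city alone.

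Four stronger readings are tempting and not supported:

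- **That the 6:6 statement contradicts randomisation within city.** It omits city, but it cites the same Fig 2 as Study area and settings, and three cities at 2:2 make 6:6. Read as unrestricted, only 216/924 = 23% of allocations would be 2:2 in every city, but the sizing of both arms in each location speaks against that reading.
- **That school type will often be fully confounded with arm.** That is frequent only inside a single city. Over the whole trial it occurs in 2/216 allocations.
- **That imbalance by type would by itself produce an apparent effect of the target size.** That needs an assumed difference between types and an unadjusted contrast.
- **That grade mix is badly uneven.** As worded, the four classes are drawn from one pool over four grades. With 3 sections per grade (assumed), 3⁴/C(12,4) = 81/495 = 16% of schools would include all four grades; with 2 sections, 16/70 = 23%; with 4, 256/1820 = 14%; with one, all would. The section count is not given, one class per grade is a possible reading, and the figure describes single schools, not a difference between arms.

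**Conclusion.** The point holds as a design weakness of moderate weight. The stated allocation rule leaves school type to chance although the sampling makes balance exactly attainable. Trial-wide imbalance has probability 59%, mostly as 4:2, and school type coincides with arm in at least one city with probability 70%. These probabilities are exact given 2:2 allocation per city, which is implied and not stated. The size of any shift in the estimate rests on an assumed difference between school types and would be smaller after baseline and covariate adjustment. The result would not be systematically biased. Grade mix is a secondary matter of wording.

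**What to change.** **If allocation has not been made:** state one scheme in which, in each city, one government and one private school go to each arm. Include city and school type in the GEE model. Reword Sampling strategy for randomized controlled trial so that its 6:6 split is described as 2:2 within each city.

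**If allocation has been made** (recruitment started on 01/11/2025): report how it was done and name school type as a covariate. If Figs 2 or 3 already show allocation by type, say so in the text.

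**Secondary:** draw one class per grade in each school, or adjust for grade.

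**Cost:** a revised allocation list if still possible, a few sentences, and one more cluster-level term in a model with 12 schools. The number of possible allocations falls from 216 to 64. The article plans no randomisation test; if one were used, its smallest two-sided P would rise from 2/216 = 0.009 to 2/64 = 0.031. That is still below 0.05, but the next step, 4/64 = 0.0625, is not, so only the most extreme result could be significant at 0.05.

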**Fig 2 pone.0354663.g002:**
[figure not shown]
Implementation plan for the study.

### Participants

The study focuses on adolescents, specifically school students in the 9^th^, 10^th^, 11^th^, and 12^th^ grades (aged 14–17 years). The inclusion and exclusion criteria for the enrolment of study participants are described below:

#### Inclusion criteria.

School-going adolescents aged 14–17 years, encompassing all genders.Adolescents who provide their assent along with parental consent to participate in this study.Adolescents who have access to smartphones/laptops/tablets and social media accounts.

#### Exclusion criteria.

Students who do not have access to smartphones or internet access.An adolescent having been diagnosed with mental health problems or other chronic medical diseases.Adolescents who refuse to participate in the study.

### Trial registration and status

Clinical Trial Registry-India, CTRI/2024/11/077115, originally registered on 11/11/2024. The study has not yet generated results. Recruitment started on 01/11/2025 and will be completed tentatively by  31/12/2026. Data collection will be completed on 30/06/2027, and results are expected by 31/12/2027.

### Ethical approval and consent to participate

This study is part of a proposal approved by the Institutional Ethical Committee, Postgraduate Institute of Medical Education and Research (PGIMER), Chandigarh, India (IEC no. IEC-04/2024-3084, dated 14/10/2024). Prior to participation, written assent will be sought from all students, while written informed consent will be sought from their parents or legal guardians.

## Implementation plan

The social marketing intervention, implemented within the framework of a randomized controlled trial, will be carried out in three distinct phases (Fig 2):

1. Pre-intervention phase2. Intervention phase3. Post-intervention phase

### Phase 1: Pre-intervention phase

The baseline assessment will be done to estimate the time spent on social media, alcohol usage, adverse child-family relationships, and sexual behavior among adolescents.

#### Sample size for baseline assessment.

For Phase 1 (baseline assessment), the sample size is calculated using the formula n = 4pq/d^2^ [9]. Where n is the sample size for each area of Tricity, p is the prevalence, q is 1-p, and d is precision. The proportion of adolescents in India is approximately 20% [10]. The prevalence of alcohol consumption among adolescents at least once a year ranged from 10.6% to 32.9% [11]. *Prevalence of sexual activity ranged between 16.9%* [12] *to 21%, and sizable numbers of Indian adolescents were facing parent-child conflicts. Therefore,* assuming a prevalence of 20%, a precision of 4%, and an attrition rate of 5%, the target sample size is calculated as 420 for each of the three cities. Taking an equivalent number of samples from each of the three cities, the final sample size for all three study areas is 1260.

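### The ±4-point precision claimed for each city's baseline prevalence assumes independent students, but each city's sample comes from only four schools and no design effect is applied

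*Protocol article*

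**What the plan says.** The section *Sample size for baseline assessment* states that "the sample size is calculated using the formula n = 4pq/d^2" and defines its terms: "Where n is the sample size for each area of Tricity, p is the prevalence, q is 1-p, and d is precision". The precision is therefore claimed for each city separately. The inputs and result are a prevalence of 20% together with "a precision of 4%, and an attrition rate of 5%, the target sample size is calculated as 420 for each of the three cities".

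The section *Sampling strategy for baseline assessment* then says where these students come from: "In total, 1260 adolescents will be recruited from 12 schools (4 schools per city) across three cities in Northern India". Each city has two government and two private schools and 105 students per school, reached by randomly selecting four classes from grades 9 to 12, with an assumed class size of 25 to 35.

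The section *Phase 1: Pre-intervention phase* gives the purpose as estimating social media time, alcohol use, family relationships and sexual behaviour, so precision is the design target of this phase. The text shown contains no ICC and no design effect, and it does not qualify the 4% for clustering.

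**The concern.** The formula is valid when students are sampled independently. Students in one school share catchment, fees, peer group and staff, so their answers on alcohol, sexual behaviour and family life are likely to be correlated. Four schools per city then carry less information than 400 independent students, and the shortfall grows with the number taken from each school.

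What is at stake is how the baseline prevalences are read. A reader who takes the sample-size section at its word will believe that each city's prevalence is known to within 4 points. If the ICC is anything but negligible, it is known less well than that.

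**Working it through.** **Inputs from the protocol.** Prevalence p = 0.20, half-width d = 0.04, multiplier 2 (the 4 in the formula is 2²), attrition 5%, 4 schools per city, 105 recruited per school. After 5% loss this is taken as 100 evaluable per school and 400 per city.

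**Input not in the protocol.** The school-level ICC is an assumption, shown as a range.

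**1. The plan's own figure.** n = 4 × 0.20 × 0.80 / 0.04² = 400, and 400 × 1.05 = 420. It reproduces exactly, so no design effect is hidden in it. (Dividing by 0.95 instead gives 421.05, or 422 rounded up, which is a trivial difference.)

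**2. How much clustering the claim tolerates.** With 400 evaluable students the half-width under independence is 2 × √(0.16/400) = 0.040, which leaves no margin. If all 420 were evaluable, the largest design effect that keeps ±4 points is 420/400 = 1.05. Setting 1 + 104 × ICC = 1.05 gives ICC = 0.05/104, about 0.0005.

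**3. Precision per city under clustering.** Design effect DE = 1 + 99 × ICC; effective n = 400/DE; SE = √(0.16 × DE/400). The last column uses the t quantile on 2 df, 4.30: four schools less two school-type strata.

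| Assumed ICC | DE | Effective n | 2-SE half-width (points) | Half-width, t on 2 df (points) |
|---|---|---|---|---|
| 0.005 | 1.495 | 268 | 4.9 | 10.5 |
| 0.01 | 1.99 | 201 | 5.6 | 12.1 |
| 0.02 | 2.98 | 134 | 6.9 | 14.9 |
| 0.05 | 5.95 | 67 | 9.8 | 21.0 |
| 0.10 | 10.9 | 37 | 13.2 | 28.4 |

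For example, at ICC 0.02 the SE is √(0.16 × 2.98/400) = 0.0345; 2 × 0.0345 = 0.069 and 4.30 × 0.0345 = 0.149.

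**4. More students in the same schools would not cure it.** With four schools the effective n stays below 4/ICC, so at an ICC of 0.01 or more it cannot reach 400. At 100 evaluable students per school, keeping ±4 points per city on the 2-SE scale would need 400 × DE = 796, 1,192 or 2,380 evaluable students at ICC 0.01, 0.02 or 0.05. That is about 8, 12 or 24 schools per city.

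**5. Pooled over the three cities.** With 1,200 evaluable students in 12 schools, SE = √(0.16 × DE/1200). The 12 schools in 6 city-by-type strata leave 6 df (t = 2.45).

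| Assumed ICC | 2-SE half-width (points) | Half-width, t on 6 df (points) |
|---|---|---|
| 0.01 | 3.3 | 4.0 |
| 0.02 | 4.0 | 4.9 |
| 0.05 | 5.6 | 6.9 |

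**The case against.** Several points on the other side are sound.

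- **The calculation is not wrong.** A reader might infer that 420 is an arithmetic error. It is not; it follows exactly from the stated formula and inputs. The mismatch is between the formula and the sampling design.
- **No between-city comparison is planned.** One might go on to say that false differences between cities will be reported. The document plans no such comparison, and it does not say that baseline intervals will ignore schools. How those intervals are computed may be settled in an analysis plan not shown. What remains is the precision claim itself, which is stated here and defined per city.
- **The trial comparison is not touched.** A reader might carry this shortfall over to the power of the trial. *Sample size for the intervention phase* has its own calculation, which gives 1,248 and is raised to 1,260 to match the baseline. Nothing here shows that figure to be right or wrong.
- **The size depends on an unknown ICC.** This stands. From ICC 0.005 to 0.10 the per-city 2-SE half-width runs from 4.9 to 13.2 points. Only the direction is certain, for any ICC above about 0.0005.
- **The government/private split may help.** It may remove some between-school variance, in which case the relevant ICC is the one within school type, and it may lie low in the range. Against that, selecting classes can add clustering of its own, and stratifying leaves fewer degrees of freedom. The text does not say that every student in a selected class is taken: four classes of 25 to 35 hold 100 to 140 students, for 105 places.

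The planned generalized estimating equations do not answer the point. They are described for changes in outcomes over time, not for the precision of baseline prevalences in a city.

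**Conclusion.** The point holds as a mismatch between design and assumption. The protocol promises ±4 points for each city from a formula for independent students, and it samples those students from four schools per city with no allowance for clustering. That precision is not delivered for any non-trivial positive school ICC.

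At assumed ICCs of 0.01 to 0.05 the per-city half-width is roughly 1.4 to 2.4 times the stated one on the plan's own scale (5.6/4 to 9.8/4). It is about three to five times as wide once the interval reflects that only four schools, in two strata, support it. These sizes assume 100 evaluable students in every school, a prevalence of 20% and one ICC across schools.

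The consequence is limited to how far the descriptive baseline prevalences can be trusted. It alters neither the number of students nor the treatment comparison, but the figure is wrong as written and easily corrected.

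**What to change.** Keep 1,260 students and 12 schools. In *Sample size for baseline assessment*:

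- Replace the per-city 4% claim with a precision statement that names the assumed ICC, the number of evaluable students per school and the degrees of freedom.
- Preferably make the pooled three-city estimate the one with a stated precision, for example about ±4.0 points on the 2-SE scale, or about ±4.9 points with 6 df, at an assumed ICC of 0.02. Show the range over 0.01 to 0.05 beside it.
- If city-level prevalences are also reported, describe their precision as low and give the wider half-widths with their ICC and 2 df.

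Compute baseline intervals with school as the primary sampling unit and, if school type is used as a stratum, with the matching degrees of freedom. Report the observed ICCs, so that the assumption can be checked.

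The cost is a few sentences and a survey-design setting in the analysis. The downside is that the reported intervals will be wider than the current text suggests.
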